## Abstract

**Background:**

Osteoarthritis of the knee is a major cause of disability among adults. Electro-acupuncture is considered a potentially useful treatment for osteoarthritis. The purpose of this study is to assess the efficacy of electro-acupuncture on pain control, pain perception, plasma cortisol and beta-endorphin levels, patient-perceived quality of life, and pain medication use in patients with chronic knee pain.

**Methods/design:**

This study is a placebo-controlled, randomized, double-blind, parallel design trial. One hundred sixty out-patients who are more than 50 years old and who have osteoarthritis of the knee will be recruited from the island of Mallorca, Spain. Each participant will be randomly placed into one of two groups: (sham) electro-acupuncture non-insertion technique and real electro-acupuncture.

Acupuncture treatments will be the Traditional Chinese Medicine type. The patients will be evaluated after a period of 1 month (with two weekly sessions), 3 months (with one monthly session), 6 months (with one session every 45 days), and 1 year later with follow-up sessions at the end of the study (with one session every 2 months).

The primary outcomes will be based on the observed changes from the baseline of the visual analogue scale (VAS) and the Western Ontario and McMaster Universities Osteoarthritis Index (WOMAC) for pain measured at 12 weeks after the end of treatment.

Also to be included in the study are the possible changes in the secondary efficacy variables from baseline as assessed by the Short Form 36 version 2 health survey (patient-perceived quality of life), patient plasma cortisol and beta-endorphin levels at the different treatment stages, the Goldberg Anxiety and Depression Scale, pain medication use, functional capacity and stiffness (WOMAC subscales), and a VAS. These variables will be assessed at 1 month, 3 months, 6 months, and 1 year after study commencement.

**Discussion:**

The findings from this study will help to determine whether electro-acupuncture is effective for chronic knee pain management in older people and whether electro-acupuncture can deliver results for the improvement of pain relief, stiffness, and disability. The study will therefore be a major step toward understanding the roles of the hypothalamic-pituitary-adrenal axis and the endogenous opioid system in the effectiveness of electro-acupuncture for chronic pain.

**Trial registration:**

ClinicalTrials.gov identifier NCT02299713 (11 Nov. 2014).

## Background

Osteoarthritis (OA) is the most common form of arthritis [1, 2]. Its prevalence is greater among women than men [3, 4]. Several factors contribute to the risk of OA, including age, gender, genetics, behavioral influences, obesity, injury, and reduced muscular strength [5]. Significant consequences of OA are activity limitations, reduced participation in work and social activities, and mental distress.

The most recent clinical guidelines based upon evidence from the UK National Institute of Clinical Excellence [6] and the Osteoarthritis Research International (OARSI) suggest that the treatment for OA be multidisciplinary in nature and consider non-pharmacological treatment (such as education, aerobic and resistance exercises, and weight loss) as well as pharmacological treatment options (paracetamol) when an additional treatment is required. In an OARSI systematic review, five of the eight guidelines considered acupuncture to be one of the 12 possible non-pharmacological therapy modalities for OA [7].

Acupuncture has been demonstrated to be a safe treatment with a low risk of serious side effects [8–12]. OA guidelines [13, 14] emphasize treatment safety as an important issue, especially when the therapeutic agents for elderly patients with knee OA and comorbidities are concurrent drugs that could have serious, life-threatening interactions.

Acupuncture could be used to explain the roles that the hypothalamic-pituitary-adrenal (HPA) axis and the endogenous opioid (EO) system play as important mediators of pain, the stress response, and other stimuli [15]. Recent neuroimaging studies by positron emission tomography have shown that the relationship between the neurochemical imbalance in the EO system [16] and the long-term pain relief produced by acupuncture practice has the opposite results of those observed with placebo (sham) acupuncture and that only acupuncture exerts a long-term effect through the EO system [17].

The effect of acupuncture on the HPA system is far from clear. Although cortisol release is one of the consequences of HPA system activation, different studies have shown opposite responses of cortisol release in response to acupuncture. One mediating factor may be the presence or absence of anxiety and depression, which are known to predict the onset and severity of chronic pain [18].

Although many studies have demonstrated the efficacy of acupuncture in the treatment of OA-associated knee pain [19], only one study [20] demonstrates the effectiveness of electro-acupuncture (EA) for pain reduction that includes the indicative reduced cortisol levels and elevated blood beta-endorphins within the same patient group. It would be of great interest to determine whether the lack of these kinds of results could be masked by interfering factors such as anxiety and depression.

When acupuncture was compared with some control groups (waiting list and control groups with active treatment), the positive effects reached the threshold of clinical relevance. Moreover, the only non-pharmacological therapeutic treatment for OA shown to reduce pain and improve physical function was exercise, and this treatment either closely met or exceeded the threshold for clinical relevance [21].

Although many studies show the efficacy of acupuncture for OA pain, the lack of a common methodology for the trial design complicates the possibility of comparing the respective results in order to determine treatment efficacy.

In this work, we have collected the following methodological suggestions for acupuncture studies that would minimize the design biases: the number of patients recruited to achieve the significant differences, treatment number, long-term treatment [22, 23], recruitment blinding method, EA use [24, 25], assessment of patient perceptions about the type of technique used before and after treatment [26], the objective and subjective assessment of the technique, and finally the use of sham with no needle penetration (a non-penetrating sham control). Thus, our aim is to apply these methods to verify the effectiveness of acupuncture for OA pain. Furthermore, our placebo use would permit the validation of the hypothesis.

Additionally, the current economic reality that dictates the need to develop favorable cost-benefit therapies for both patients and the health-care system should not be overlooked, and acupuncture is a cost-effective therapy for the treatment of knee OA [27].

Finally, a great deal of evidence indicates that various possible physiological mechanisms explain how acupuncture may provide pain relief, and these indicate that further research is needed to clarify the interrelationship and regulation of these mechanisms.

Although cortisol release is one of the consequences of HPA system activation, some studies have shown responses opposite to the cortisol release produced by acupuncture practice. Normal individuals show opposite cortisol responses to those with chronic pain conditions. This suggests that if the HPA axis contributes to the efficacy of acupuncture, its role is more complex than simply deactivating this system. Rather the contribution may depend on the population being studied. One of the objectives of this study is to provide more data to elucidate possible mechanisms of action and to show correlations between reductions in pain and changes in hormonal markers of HPA axis function. This will aid in establishing whether changes in HPA axis are causal or merely epiphenomenal in treatment efficacy.

This following study is a project to assess the effectiveness of EA for the treatment of common pathologies that involve chronic OA pain in knee. Additionally, it will evaluate pain perception, plasma endorphin and cortisol levels, patient quality of life, and the need for pharmacological drugs regardless of whether EA is applied.

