### Statistical analysis

The results will be analyzed by using the SPSS statistical software version 18.0. A descriptive analysis of the collected data will be obtained by using the mean, the standard deviation, and the maximum and minimum values for the quantitative variables that follow a normal distribution. For variables without a normal distribution (degree of pain, plasma levels, and quality of life, among others), the median, the 25th and 75th percentiles, and maximum and minimum values will be calculated.

Qualitative variables will be expressed as frequencies and percentages. Differences shall be detected by chi-square or Fisher tests for categorical variables and Student *t* or Mann-Whitney tests for the resultant variables.

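### Pain–hormone correlations are said to help decide whether HPA-axis changes are causal, which a correlation cannot do

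*Protocol article*

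**What the plan says.** In the protocol article's Background, the paragraph on cortisol sets one objective as providing more data on mechanisms and "to show correlations between reductions in pain and changes in hormonal markers of HPA axis function". The next sentence states what this is for: "This will aid in establishing whether changes in HPA axis are causal or merely epiphenomenal in treatment efficacy".

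The Background also names a factor that could act on the hormone results. On the cortisol response it says "One mediating factor may be the presence or absence of anxiety and depression". On the scarcity of earlier positive hormone findings it names one question as interesting: "determine whether the lack of these kinds of results could be masked by interfering factors such as anxiety and depression".

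Under Statistical analysis, categorical variables are to be compared by chi-square or Fisher tests, and other variables by the Student t test "or Mann-Whitney tests for the resultant variables". No method for the correlations appears there. GADS is listed under Secondary variables as an outcome, and Table 1 schedules it at visit 0 and at each follow-up assessment. The article gives it no role as a covariate, stratum or effect modifier.

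**The concern.** The article draws a causal reading from a quantity that does not carry one. Pain reduction and hormone change are both measured after randomisation, and neither is assigned by the design. They can move together for at least three reasons: the hormone acts on pain; treatment shifts both by separate routes; or a patient characteristic drives both. The second and third are the epiphenomenal case that the sentence hopes to rule out, yet all three produce a correlation.

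The between-group tests do not fill the gap. A difference between arms in cortisol and a difference between arms in VAS, each tested alone, say nothing about how the two are linked.

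At stake is the mechanistic conclusion. A correlation induced by treatment or by anxiety and depression could be presented as evidence on the role of the HPA axis, which the article puts forward as a main contribution of the trial.

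**Working it through.** **Inputs from the protocol article (Participants).** VAS difference 3, SD 4, hence standardised effect 3/4 = 0.75; two-sided alpha 1%; beta below 5%; attrition 20%; 80 per group.

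**Reproducing the stated sample size.** n per arm = 2(2.576 + 1.645)²/0.75² = 2 × 17.81/0.5625 = 63.3, so 64. Allowing for attrition, 64/0.80 = 80 per arm, 160 in all. The stated figure reproduces. It concerns VAS only and is used here just to supply 64 completers per arm and the 0.75 SD pain shift.

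**Assumed, because the article gives no figure.** The hormone shift *d* (0.2 to 0.75 SD), pooling of the two arms, and the strength of any common factor.

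**Step 1: treatment moves both, with no link within arms.** With equal arms, within-arm SDs of 1, a pain shift of 0.75 and a hormone shift *d*, the pooled correlation is

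r = 0.25 × 0.75 × d / √[(1 + 0.25 × 0.75²)(1 + 0.25 × d²)].

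For d = 0.75: r = 0.1406/1.1406 = 0.12. For d = 0.3: r = 0.0563/√(1.1406 × 1.0225) = 0.052.

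Rejection rates at 5% with n = 128 come from the Fisher z approximation, z = atanh(r) × √125, and from 40,000 simulated trials per row:

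| Hormone shift (SD) | Pooled r | Fisher z | Simulated, pooled | Simulated, arm-adjusted |
|---|---|---|---|---|
| 0.2 | 0.035 | 6.8% | 6.8% | 5.1% |
| 0.3 | 0.052 | 9.0% | 9.1% | 4.9% |
| 0.5 | 0.085 | 15.9% | 16.0% | 5.1% |
| 0.75 | 0.123 | 28.3% | 28.9% | 4.9% |

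**Step 2: a true mediator against a common factor.** Two models are compared, each with total shifts of 0.75 SD in hormone and pain.

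- Causal: the hormone acts on pain with slope 0.5.
- Common factor: the hormone has no effect, but a GADS-type factor, measured without error, gives a within-arm correlation of 0.5.

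In both, pooled r = (0.5 + 0.1406)/1.1406 = 0.56. Simulation (2,000 trials, 64 per arm) gives:

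| Truth | Raw r | Hormone coefficient given arm | Given arm and baseline GADS |
|---|---|---|---|
| Hormone causal | 0.56 | 0.50 | 0.50 |
| GADS-type factor drives both | 0.56 | 0.50 | 0.00 (significant in 4.8%) |
| Unmeasured factor drives both | 0.56 | 0.50 | 0.50 (significant in 100%) |

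The between-arm t-tests on hormone and on pain were each significant in about 99% of trials in all three rows, so they do not discriminate.

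**Step 3: order of measurement.** Under the heading for the 1-month visit, the pain forms are completed before that day's treatment. Under Baseline visit, post-baseline blood is drawn 5 minutes after the session. At 1 month the supposed mediator is therefore sampled after the outcome.

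**The case against.** The strongest reply is that much of this argues from silence. The article says only that correlations will be shown. A reader might infer that they will be raw and pooled across arms, but the text does not say so. The Statistical analysis section is a short summary that names no correlation method at all, so its list of tests is plainly not exhaustive. A mediation, adjustment or interaction model may properly sit in a fuller plan. This stands: the absence of such a model is not the point made here.

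Other tempting readings also go too far.

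- A reader might take the masking question (whether hormone results "could be masked by interfering factors such as anxiety and depression") as a trial objective. It is voiced as an interest in the Background and does not appear among the hypotheses or the listed variables.
- A reader might conclude that the stated tests ignore GADS. They do apply to it as a secondary outcome; what is absent is any adjusting role.
- The causal sentence is hedged. It speaks of aiding in establishing causality and does not claim proof.

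The upper figure of 29% also depends on a 0.75 SD hormone shift borrowed from the VAS calculation. At 0.2 SD the excess over 5% is small. Adjustment is no cure either: with an unmeasured common cause the coefficient stays at 0.50.

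What survives is the stated inference. No unseen plan alters a published sentence saying that correlations bear on whether HPA changes are causal. The limits of adjustment are a further reason to change that sentence.

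**Conclusion.** The point holds as a stated inference that the planned quantity cannot support. Correlations between pain reduction and hormone change do not distinguish a causal from an epiphenomenal HPA change. The named between-group tests do not relate hormone to pain, and baseline GADS has no stated adjusting role although the Background names anxiety and depression as possible interfering factors.

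If arms were pooled, a correlation with no within-arm basis would be significant at 5% in about 9% to 29% of trials. This rests on 64 completers per arm, the design pain shift of 0.75 SD and assumed hormone shifts of 0.3 to 0.75 SD. With a strong common factor, raw r is 0.56 whether or not the hormone is causal.

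The documents do not support saying that the trial will report a spurious causal finding. The primary VAS comparison, its alpha and its sample size are not affected.

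**What to change.** 1. In the Background, replace the causal sentence with a statement that the study will explore whether hormone changes are associated with pain reduction.
2. Estimate that association adjusted for arm and for baseline GADS anxiety and depression scores.
3. Compare hormone change between arms adjusted for baseline hormone and baseline GADS, in place of the unadjusted t or Mann-Whitney comparison.
4. Label any arm-by-GADS term exploratory. With 64 per arm and unit residual SD, the slope difference has a standard error of about √(2/64) = 0.177. An assumed difference of 0.3 SD per SD of GADS would then be detected with only about 40% power (0.3/0.177 = 1.70, against 1.96).
5. State two limits: adjustment does not establish causation, because an unmeasured common cause would remain; and at 1 month the blood sample follows the session while the pain forms precede it.

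The cost is one reworded sentence and some analysis work. Baseline hormone and GADS are already collected at visit 0, so no new data, visits or samples are needed.

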### Hypothesis

#### Conceptual hypothesis

Patients who receive EA will have, to some degree, better pain control than non-treated patients.

#### Operative hypothesis

Patients who receive EA will have a measured basal pain perception that is three points less on the visual analogue scale (VAS) after EA treatment in comparison with non-treated patients.

#### Statistical hypothesis

Practice of EA will result in a statistically significant control of pain compared with the pain levels of non-treated patients.

## Methods/design

### Trial design

This study proposes a randomized, double-blind, placebo-controlled, pre- and post-test, parallel design clinical trial which conforms to the CONSORT (Consolidated Standards of Reporting Trials) [28] and STRICTA (Standards for Reporting Interventions in Clinical Trials of Acupuncture) guidelines [29] for acupuncture studies (Fig. 1).

**Fig. 1 Fig1:**
[figure not shown]
Trial flow. The study trial flow is described, indicating the patient selection process, treatment, and follow-up. *Visual analogue scale, Western Ontario and McMaster Universities Osteoarthritis Index, Short Form 36 version 2 health survey, blood sample collection, Goldberg Anxiety and Depression Scale, and medication use are measured on each follow-up visit. EA, Electro-acupuncture

### Participants

Participants will be selected from a population with knee chronic pain caused by OA (>3 months in duration), from the communities of the island of Mallorca (Balearic Islands, Spain). These participants will be recruited in the outpatient clinics of the island’s hospitals and advertisements in local newspapers and through the hospital website (http://www.hsll.es). Advertisements for patient recruitment will not specify acupuncture as one of the treatments being investigated or offered. Doctors from the trauma services of local hospitals will be invited to screen patients. The clinical trial will be performed by the Pain Unit at Son Llàtzer Hospital, Palma de Mallorca.

A total of 160 patients will be necessary (80 subjects for each treatment group) to detect differences of at least three points in the pain perception assessment according to VAS (scale of 0 to 10). Accepted values will be for an alpha risk of 1 % and beta risk of less than 5 % in a bilateral contrast as well as a value of 4 for the standard deviation (size effect of 0.75). It is assumed that 20 % of the trial patients will be lost to attrition. Patients will be included in the study by case-consecutive, non-probability sampling after responding to a recruitment visit to the Pain Clinic; then if they sign an informed consent form, they will be placed randomly into one of the treatment groups [30].

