### Removal criteria

Patients will be removed by voluntary removal or by failure to consecutively attend two or more EA sessions.

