#### Secondary variables

Secondary variables to be considered are the following: the change in the secondary efficacy variables from the baseline of the Short Form 36 version 2 health survey (SF-36v2) (patient-perceived quality of life), the change in plasma cortisol and beta-endorphin levels, the scores for the Goldberg Anxiety and Depression Scale (GADS), changes in pain medication use, changes in functional capacity and stiffness (WOMAC subscales), and VAS scores measured at 1 month, 3 months, 6 months, and 1 year after study commencement.

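### The two-group test named for 12-week pain leaves out the month-1 scores of patients who drop out, so it can be biased if response-related dropout differs between arms

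*Protocol article*

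**What the plan says.** All references are to the protocol article.

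- **Participants** sizes the trial "to detect differences of at least three points in the pain perception assessment" on a 0 to 10 VAS, with SD 4 and "an alpha risk of 1 % and beta risk of less than 5 % in a bilateral contrast". It assumes that 20% "of the trial patients will be lost to attrition" and arrives at 80 per arm. It does not say by what time the 20% is lost or how it splits between arms.
- **Main variables** sets the primary outcomes as change from baseline in VAS and WOMAC pain at 12 weeks. I take this to be the month-3 visit of Table 1.
- **Secondary variables** lists "VAS scores measured at 1 month, 3 months, 6 months, and 1 year after study commencement". Table 1 and the section on the 1-month visit confirm that VAS and WOMAC are scored at month 1.
- **Statistical analysis** names Student t or "Mann-Whitney tests for the resultant variables" for continuous outcomes. It mentions no longitudinal model and no handling of missed visits. The one missing-data rule, under Baseline visit, concerns single unanswered WOMAC items.
- **Removal criteria** states: "Patients will be removed by voluntary removal or by failure to consecutively attend two or more EA sessions".
- **Retention** is addressed elsewhere. The Procedure and Control group sections describe efforts to keep patients in follow-up, and Table 1 records reasons for dropout at months 1, 3, 6 and 12.

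**The concern.** Enrolling more patients protects the power of the comparison. It does not make the patients who remain in one arm comparable with those who remain in the other.

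A two-group test of the 12-week change needs a 12-week score. A patient scored at baseline and month 1 who then leaves contributes nothing, although the month-1 score says something about how that patient was doing. The article itself connects slow benefit with dropout: under Control group it says that results take time to show and that follow-up is needed to prevent dropout. Suppose sham patients who feel no benefit leave more often than EA patients do. The remaining sham patients then look better than the sham arm as a whole, and the estimated benefit of EA shrinks. At stake are the primary estimate and the power that the sample size was meant to secure.

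**Working it through.** **1. The plan's own figure.** With difference 3, SD 4, two-sided alpha 1% and power 95%:

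n per arm = 2 × (2.576 + 1.645)² × 4² / 3² = 63.3, rounded up to 64. Then 64 / 0.8 = 80 per arm, 160 in total. This matches the article exactly. Power with 64 per arm is 0.952 by the normal formula, so the comparison is sized on those expected to remain.

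**2. Assumptions for the bias check (none is in the article).** Change scores have SD 4 at months 1 and 3, with correlation r of 0.5 to 0.7 between the visits. Everyone has a month-1 score, and loss between then and month 3 depends on that score. Negative change means less pain.

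**3. One shared dropout rule.** The log-odds of leaving rise by 1 per SD of worse month-1 change, identically in both arms, with 20% lost overall. The effect is 3 points at both visits. Because EA patients do better, loss is 15% in EA and 25% in sham.

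| r | EA completers | Sham completers | Difference | Bias | Using month-1 score |
|---|---|---|---|---|---|
| 0.5 | −3.26 | −0.43 | −2.83 | 0.17 | −3.00 |
| 0.7 | −3.38 | −0.60 | −2.78 | 0.22 | −3.01 |

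About 68 and 60 patients remain, so SE = 4 × √(1/68 + 1/60) = 0.71. Power is Φ(2.83/0.7085 − 2.576) = 0.92 and Φ(2.78/0.7085 − 2.576) = 0.91. A smaller month-1 effect would make the split, and so the bias, smaller.

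**4. Only sham non-responders leave, 20% lost in each arm by week 12.** Here the month-1 effect is 2 points and EA dropout is random (4000 simulated trials per scenario).

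| Sham odds ratio per SD | r | Completers' difference | Power at 1% |
|---|---|---|---|
| 2 | 0.5 | 2.74 | 0.90 |
| 2 | 0.7 | 2.64 | 0.87 |
| 3 | 0.5 | 2.64 | 0.87 |
| 3 | 0.7 | 2.47 | 0.82 |

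The bias is therefore 0.26 to 0.53 points. Hand check of the extremes: SE = 4 × √(2/64) = 0.707; Φ(2.74/0.707 − 2.576) = 0.90 and Φ(2.47/0.707 − 2.576) = 0.82. An estimate that also uses the month-1 score gives 2.99 to 3.02 throughout.

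**5. Less loss by week 12.** Under the same sham-only pattern:

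- 10% lost: estimate 2.72 to 2.87, power 93% to 96%.
- 5% lost: estimate 2.86 to 2.93, power 96% to 97%.

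**6. Where there is no bias.** Random dropout gives none, even at 10% versus 30%. Equal response-related dropout at 20% in both arms gives none. The same response-related slope with 10% versus 30% gives 0.31 to 0.46, so equal rates are part of that condition. Under random dropout the model's variance is about 4% to 11% below that of the completers' test.

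**The case against.** The strongest objection is that this is an ordinary missing-data matter for an analysis plan that is not shown. A short article need not give an analysis set or a missed-visit rule, and a t test could be run on imputed values. That stands as far as it goes: the absence of such a rule is not the point here. What remains is that the article does name its tests and sizes the trial on those who stay. Applied as written, those tests discard scores that the trial collects.

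A reader might draw four stronger conclusions that the article does not support:

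- **That it states a completers-only analysis.** It does not say that leavers are excluded, kept or imputed. This is inferred from the named tests.
- **That attrition is met only by extra enrolment.** Retention efforts and recorded reasons for dropout are also planned. Inflation is only the sole *statistical* provision, and recording reasons changes no estimate.
- **That the primary difference is biased.** It is biased only if dropout is related to response and differs between arms in rate or pattern. The 20% is also not tied to week 12 in a trial that runs for a year, so the power figures of 82% to 90% are for the case where all of it is lost by then.
- **That EA is more likely to be declared effective by chance.** With no true effect and sham-only dropout at odds ratio 3, the 1% test rejected about 2% to 4% of the time, but almost always in favour of sham. With the same rule in both arms, the rate returned to 1.1% to 1.2%. Where patients are blinded and there is no effect, a shared rule is the more natural assumption.

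The recovery of 3.0 by the model also needs care. The simulations let dropout depend only on a month-1 score that everyone has, which is the model's own assumption. Eight of the ten sessions up to month 3 fall in month 1, so some removals may come before any post-baseline score.

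**Conclusion.** The point holds in conditional form, as a cheap improvement to a stated method. The sample size is correct on its own inputs and needs no change.

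With a true effect of 3 points, the completers' comparison understates it by about 0.2 points (roughly 6% to 7%) under one shared response-related dropout rule. It understates it by about 0.3 to 0.5 points if only sham non-responders leave and the full 20% is lost by week 12. The bias shrinks with lower early loss. It is zero if dropout is random, or equally response-related in both arms at equal rates. Other patterns could change its size or direction. The figures rest on an assumed correlation of 0.5 to 0.7, an assumed month-1 effect of 2 to 3 points, and an assumed strength of the link between response and dropout. The article supplies none of these. Confidence is medium: the mechanism is certain, but its size in this trial is not known.

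**What to change.** Name as the primary analysis a mixed model for repeated measures, fitted separately to change in VAS and in WOMAC pain at 1, 3, 6 and 12 months. Include arm, visit and arm-by-visit terms with an unstructured covariance, and all randomised patients with any post-baseline score. Take the 12-week arm contrast as the primary estimate. Keep the t or Mann-Whitney test of patients with a 12-week score as a sensitivity analysis.

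The cost is a change of wording and some programming, best settled before unblinding. The 160 patients and the planned assessments stay as they are. The model assumes that missingness depends only on observed scores, which is a weaker assumption than the completers' test needs but still an assumption. It does not recover patients who leave before the month-1 assessment, so their number by arm should be reported.
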